**Methods/design:**

One hundred individuals between the ages of 18 and 60 who consent to undergo lumbar microdiscectomy will be recruited to participate in this study. Subjects will be randomly assigned to one of two groups: 1) one session of back care education, or 2) a back care education session followed by the 12-week USC Spine Exercise Program. The outcome examiners (evaluators), as well as the data managers, will be blinded to group allocation.

Education will consist of a one-hour "one-on-one" session with the intervention therapist, guided by an educational booklet specifically designed for post-microdiscectomy care. This session will occur four to six weeks after surgery. The USC Spine Exercise Program consists of two parts: back extensor strength and endurance, and mat and upright therapeutic exercises. This exercise program is goal-oriented, performance-based, and periodized. It will begin two to three days after the education session, and will occur three times a week for 12 weeks.

Primary outcome measures include the Oswestry Disability Questionnaire, Roland-Morris Disability Questionnaire, SF-36^® ^quality of life assessment, Subjective Quality of Life Scale, 50-foot Walk, Repeated Sit-to-Stand, and a modified Sorensen test. The outcome measures in the study will be assessed before and after the 12-week post-surgical intervention program. Long-term follow up assessments will occur every six months beginning one year after surgery and ending five years after surgery.

Immediate and long-term effects will be assessed using repeated measures multivariate analysis of variance (MANOVA). If significant interactions are found, one-way ANOVAs will be performed followed by post-hoc testing to determine statistically significant pairwise comparisons.

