The study is divided into three phases, a protocol development phase, an implementation or intervention phase, and a follow-up phase. During the protocol development phase, a team of physical therapist researchers and clinicians developed, tested, and standardized the post-surgical intervention and testing protocols. During the intervention phase, a two-group, pretest-posttest design will be used, with participants being randomly assigned to one of two groups: one session of back care education, or a back care education session followed by the 12-week USC Spine Exercise Program. This design will allow for the analysis of the effects of treatment over time. The outcome measures in the study (see below) will be assessed before and after the post-surgical intervention period. The evaluators, as well as the data managers, will be blinded to group allocation. After the end of the intervention phase, follow-up assessments of selected outcome measures will be conducted on all participants every six months, beginning one year and ending five years after the date of surgery (the follow-up phase). The follow-up phase will allow for the analysis of the stability of the effect of treatment over time.

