### Data analysis

The primary and secondary outcome measures will be assessed for immediate and long-term effects using two-factor multivariate analysis of variance (MANOVA), with repeated measures for time. For all multivariate ANOVA tests described, significant main effects will be reported if there are no significant interactions. If significant interactions are found, then one-way ANOVAs will be performed for each main effect. Post-hoc testing will be performed (as necessary) to determine statistically significant pairwise comparisons. Statistical analysis of the results will be performed using the SAS system, version 8.2 (SAS Institute Inc., Cary, NC, USA). All significance levels will be set at p < 0.05.

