### Sample size

Power calculations were based on data from prior published studies [23,24,42,44,57]. These data indicated that the inter-subject variability with respect to impairments, activity, and participation, was moderate to high. Since the outcome measures assess the immediate and long-term effects of rehabilitation in addition to surgery, the calculations were made on the assumption that the changes due to exercise and education will be greater than those expected for education alone. A 50% difference between groups (education, and exercise plus education) is expected based on prior studies, and a 30% subject attrition rate is anticipated. The possible attrition rate is attributed to length of the rehabilitative program, elimination of symptoms, or increase of symptoms and need for a second surgery. All power calculations were based on an alpha level of 0.05 and power of 0.8. Therefore, accounting for attrition, each group would need approximately 50 subjects.

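### The analysis rule uses the group-by-time interaction only as a gate, so no baseline-adjusted difference between arms is reported as the treatment effect

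*Protocol article*

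**What the plan says.** The Data analysis section sets one procedure for all primary and secondary outcomes, immediate and long-term: a "two-factor multivariate analysis of variance (MANOVA), with repeated measures for time". Two branches follow.

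- Interaction not significant: "significant main effects will be reported if there are no significant interactions".
- Interaction significant: "If significant interactions are found, then one-way ANOVAs will be performed for each main effect", then post-hoc pairwise tests as needed. The abstract repeats this branch: "one-way ANOVAs will be performed followed by post-hoc testing to determine statistically significant pairwise comparisons".

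The same threshold applies throughout: "All significance levels will be set at p < 0.05".

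Methods/design says that "a two-group, pretest-posttest design will be used", and Outcome measures lists a pre-intervention assessment, a post-intervention assessment and a 1-year assessment. Baseline therefore enters the model as a level of the time factor and not as a covariate. The hypothesis at the end of the Background is comparative: exercise plus education should produce more improvement than education alone.

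**The concern.** In a model where time includes a visit before any intervention, greater improvement in one arm is a group-by-time interaction. The plan tests that interaction, but then uses it to choose what to report.

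- **Gate not passed.** The group main effect averages the arm difference over all visits, including one where no treatment effect can exist. This dilutes a real effect and brings in chance baseline imbalance. The time main effect is also reportable, but it mixes post-surgical recovery with any treatment effect and does not compare the arms.
- **Gate passed.** A one-way ANOVA on group at a visit ignores the baseline value. A one-way ANOVA on time tests change over visits, and within one arm that is not a between-arm comparison. With only two arms, pairwise comparisons among the levels of a factor are needed only for time.

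The reported treatment effect thus depends on a preliminary test, and on neither branch is it the hypothesised contrast with baseline taken into account. Power is lost, and a change that is significant in one arm but not in the other could be read as efficacy.

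**Working it through.** **Inputs from the article.** About 50 subjects per group and 30% attrition (Sample size), so 50 × 0.7 = 35 evaluable per arm. Design values: "All power calculations were based on an alpha level of 0.05 and power of 0.8". Effect: "A 50% difference between groups (education, and exercise plus education) is expected based on prior studies", with no endpoint, scale or SD.

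**The plan's own figure.** Without an SD or endpoint, 50 per group cannot be reproduced from the stated inputs. Solving backwards, 35 per arm at two-sided 0.05 and 80% power detects (1.960 + 0.842) × √(2/35) = 2.802 × 0.239 = 0.67 SD. I use d = 0.67 as the working effect.

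**Assumptions not in the article.** Two-sided tests, normal data, equal variances, one endpoint, one pre and one post visit, within-subject correlation r = 0.3, 0.5 or 0.7.

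**Single tests.** The noncentrality is the effect divided by (SD × √(2/n)), with √(2/35) = 0.239 and the visit SD set to 1.

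- Interaction (change score): effect d, SD √(2(1−r)).
- Group main effect (mean of both visits): effect d/2, SD √((1+r)/2).
- ANCOVA on the post value: effect d, residual SD √(1−r²).
- Unadjusted one-way group test at the post visit: effect d, SD 1.

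Example at r = 0.5: interaction 0.67/(1.000 × 0.239) = 2.80; main effect 0.335/(0.866 × 0.239) = 1.62; ANCOVA 0.67/(0.866 × 0.239) = 3.24.

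| Power (noncentral t), n = 35 per arm | r = 0.3 | r = 0.5 | r = 0.7 |
|---|---|---|---|
| Interaction | 65% | 79% | 95% |
| Group main effect alone | 40% | 36% | 32% |
| Unadjusted group test, post visit | 79% | 79% | 79% |
| ANCOVA | 82% | 89% | 97% |

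**The rule followed to its end** (simulation, 40,000 trials per setting). A group effect is claimed if the interaction is not significant and the group main effect is, or if the interaction is significant and the one-way group test at the post visit is too.

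| | r = 0.3 | r = 0.5 | r = 0.7 |
|---|---|---|---|
| Power, d = 0.67 | 72.5% | 75.0% | 78.2% |
| Loss against ANCOVA, points | about 9 | about 14 | about 19 |
| False group effect, d = 0, post visit counted | 6.0% | 5.5% | 5.4% |
| False group effect, any visit counted | 7.2% | 6.4% | 6.0% |
| False positive if the interaction alone also counts | 9.7% | 9.6% | 9.8% |

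The last row agrees with theory: with equal variances the interaction and the group main effect are independent under the null, so 1 − 0.95² = 0.0975.

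The loss grows with r. A high correlation makes the interaction almost certain to be significant (95% at r = 0.7), and the rule then hands the claim to an unadjusted test whose power stays at 79% whatever r is.

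**Three visits** (pre, post, 1 year; same effect at both later visits; 35 per arm). The rule has 87 to 88% power against 96 to 99.5% for ANCOVA on the mean of the later visits. Its false group-effect rate is about 6 to 7% counting post-baseline visits, and up to 8% counting any visit.

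**The case against.** The strongest defence is that the plan does test the right thing. With pre/post data the group-by-time interaction is exactly the between-arm t-test of change from baseline, and the MANOVA tests it first. That is correct. A reader might infer that arms are never compared relative to baseline, and the article does not support that. What stands is narrower: the comparison serves as a gate, and neither branch then reports a baseline-adjusted difference.

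A reader might also infer that the rule doubles the false-positive rate. It does so only if a significant interaction is itself taken as a positive result. The article does not say what counts as success, so that reading is not excluded, but its own procedure sends a significant interaction on to further tests. Likewise, the 32 to 40% power of the group main effect is not the power of the rule, because that test is only the fallback.

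Three further readings go too far:

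- Eleven scheduled visits would give 11 × 10/2 = 55 visit pairs, but only for questionnaires and pain scales. The walk, sit-to-stand and Sorensen tests have three visits and so three pairs, and post-hoc tests are run only as needed.
- The article does not show that the one-way ANOVAs on time would treat repeated values as independent. It specifies repeated measures for time, and a one-way repeated-measures follow-up is standard.
- A one-way group test at a post-intervention visit is a valid randomised comparison. Its fault is inefficiency.

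Finally, a condensed article may leave covariates and post-hoc adjustment to the full analysis plan. That would answer a complaint about omission. The branching rule, however, is stated here and partly repeated in the abstract.

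**Conclusion.** The point holds in this form: the stated rule uses the interaction as a gate and then reports tests that are diluted by the pre-intervention visit, are not between-arm comparisons, or ignore baseline. No baseline-adjusted between-arm difference is reported as the treatment effect.

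The main cost is power: about 9 to 19 points against ANCOVA with pre/post data, which puts the rule below the 80% that the trial was designed for while ANCOVA exceeds it. The inflation of the false group-effect rate is modest.

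These sizes rest on the assumed 0.67 SD effect, 35 evaluable per arm, equal variances and correlations of 0.3 to 0.7. They are per endpoint and leave out multiplicity across the several primary outcomes. The structural fault does not depend on them.

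**What to change.** Define the treatment effect as the between-arm difference adjusted for the pre-intervention value, from ANCOVA or from an arm-by-visit contrast in a mixed model with baseline as covariate. Report it with a 95% confidence interval, at the post-intervention visit first and then at 1 year. Delete the main-effect fallback. Label within-arm changes and visit-to-visit comparisons as descriptive.

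Apply baseline adjustment only where a pre-intervention value exists. Lumbar range of motion has none, because post-surgical restrictions rule out that measurement (Secondary outcome measures).

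Up to 1 year the change costs only analysis wording and uses measurements already scheduled. Beyond 1 year wording is not enough: under Follow-up period, subjects who report no symptoms are sent only the physical activity scale, so the disability, quality-of-life and pain outcomes are not collected from them. That rule has to be resolved before a later contrast, such as one at 5 years, can be estimated.

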### Outcome measures

We have used the International Classification of Functioning (ICF) conceptual framework [31,32] to classify the study's outcome measures (Figure 6). The ICF framework categories (body functions and structures, activity, participation) correspond, respectively, to Nagi's disablement model [32,33] categories (impairments, functional limitation, disability). We divided the outcome measures into primary and secondary variables. The primary outcome measures will provide an assessment of the intervention and the secondary outcome measures are descriptive, informing, and hypothesis-building. Testing of all outcome measures will be administered at the post-surgical/pre-intervention assessment, post-intervention assessment, and 1-year post-surgical assessment. In addition, completion of questionnaires and pain visual analog scales (VASs) will occur every six months after the 1-year post-surgical assessment, for the remaining four years of the study.

The subject must complete all sections of each questionnaire for the questionnaire to be considered valid. Research personnel will ensure that all sections are completed during each assessment. Incomplete questionnaires will not be accepted for data entry.

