#### Primary outcome measures

The following survey instruments were placed in the "participation" category of the ICF: Oswestry Disability Questionnaire (OD), Roland-Morris Disability Questionnaire (RM), SF-36^® ^quality of life assessment, and Subjective Quality of Life Scale (SQOL).

The OD measures the activities of daily living most likely to be limited in people with lower back pain. The most recent version of the OD will be used, in which the question regarding sex has been replaced with one regarding employment and homemaking [34]. The RM is a short questionnaire that assesses functional intolerances related to low back pain. It is easy to administer and has been shown to be reliable [35,36] Both the OD and the RM have been used as outcome measures with patients who have undergone microdiscectomy [7,9-11,37-39].

The SF-36^® ^has been used with a variety of populations to compare the effects of different diseases and treatments, and for screening individuals' health profiles [40]. For the purposes of this study, the SF-36^® ^will be used to assess baseline quality of life for each subject before and after the intervention period. It has been used in patients with low back pain and after lumbar surgeries [37]. The SQOL [41] comprises only one item, and is used to obtain a general quality of life assessment.

The "activity" primary outcome measures will include the 50-foot Walk and Repeated Sit-to-Stand tests. The 50-foot Walk test measures the time it takes to walk a distance of 50 feet as fast as tolerated. The Repeated Sit-to-Stand test measures the time it takes to complete five consecutive repetitions of a sit-to-stand sequence as fast as tolerated. Good-to-excellent test-retest reliability has been established for these measures (ICC = 0.99 and 0.89, respectively) [42].

The "body functions and structures" (i.e., "physical") primary outcome measures will include a Modified Sorenson test and pain visual analog scales [43] (VASs). The pain VASs will be administered immediately after sitting for 10 minutes and after the 5-minute Walk test.

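### The primary outcome list differs between abstract and methods, no measure or visit decides the trial, and the MANOVA step protects the 5% level only if no measure responds

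*Protocol article*

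**What the plan says.** All references are to the protocol article.

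- **Abstract, Methods/design.** "Primary outcome measures include the Oswestry Disability Questionnaire, Roland-Morris Disability Questionnaire", then the SF-36, and then "Subjective Quality of Life Scale, 50-foot Walk, Repeated Sit-to-Stand, and a modified Sorensen test". That is seven measures, and pain is not among them.
- **Primary outcome measures.** Four questionnaires (Oswestry, Roland-Morris, SF-36, Subjective Quality of Life Scale) stand under participation. For activity, "primary outcome measures will include the 50-foot Walk and Repeated Sit-to-Stand tests". For body functions, "primary outcome measures will include a Modified Sorenson test and pain visual analog scales". On pain it adds: "The pain VASs will be administered immediately after sitting for 10 minutes and after the 5-minute Walk test". The total is eight if the pain scales count as one measure and nine if they count as two.
- **Outcome measures.** All measures are taken before the intervention, after it and at one year. Later visits collect only questionnaires and pain scales. It also says that "the secondary outcome measures are descriptive, informing, and hypothesis-building".
- **Data analysis.** Primary and secondary measures go through a two-factor MANOVA with repeated measures for time. One-way ANOVAs follow a significant interaction, with post-hoc pairwise tests as needed. "All significance levels will be set at p < 0.05".
- **Sample size.** About 50 per group, from alpha 0.05, power 0.8, an expected 50% group difference and 30% attrition. No outcome is named.

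**The concern.** Two things combine. The two lists disagree on whether pain is primary, although pain is part of the hypothesis stated in the Background. And nothing says which measure, at which visit, makes the trial positive, while every test is run at 0.05.

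An overall multivariate test followed by separate tests gives what is called weak control: it limits error when there is no effect on anything. It does not limit error on the unaffected measures once one affected measure has opened the gate. That situation is plausible here. The back-extensor programme is built around holding the Sorensen position for 180 seconds and ends with the modified Sorensen test, which is itself a primary outcome. A gain on the trained test could therefore open the way to a chance finding on disability, quality of life or pain, reported as a primary result at a nominal 5%.

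**Working it through.** **1. The plan's own figure.** The 50 per group cannot be rebuilt forwards, because no SD or outcome is given. Working back:
- completers per group = 50 × (1 − 0.30) = 35
- detectable standardised difference, two-sided (sidedness is not stated): d = (1.960 + 0.842) × √(2/35) = 0.67

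These two values are used below.

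**2. Separate tests without the MANOVA step, no true effect, one visit.** Independent measures: 1 − 0.95^k.
- k = 7: 30.2%
- k = 8: 33.7%
- k = 9: 37.0%

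Simulated at correlation 0.3, 0.5 and 0.7: k = 7 gives 27.4%, 22.2% and 17.5%; k = 9 gives 32.2%, 26.9% and 20.1%. The range is about 17 to 37%.

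**3. With the MANOVA step, no true effect.** Simulation with 35 per group and 20,000 runs. A Hotelling T² test at 0.05 over all primaries at one visit stands in for the interaction test, followed by t-tests at 0.05. The gate opens in about 5% of trials, and a false positive on at least one measure follows in about 3 to 5%. Two independent MANOVAs (immediate and long-term) would give at most 1 − 0.95² = 9.75%.

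**4. With the MANOVA step, one measure truly affected.** Chance that the gate opens and at least one of the other 6 to 8 measures is falsely significant:

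| Primaries | Correlation | d = 0.67 | d = 1.2 |
|---|---|---|---|
| 7 | 0.3 | 18.5% | 23.9% |
| 7 | 0.5 | 18.4% | 21.0% |
| 7 | 0.7 | 16.5% | 16.7% |
| 8 | 0.3 | 20.2% | 27.5% |
| 8 | 0.5 | 19.7% | 23.1% |
| 8 | 0.7 | 17.0% | 17.9% |
| 9 | 0.3 | 21.3% | 29.6% |
| 9 | 0.5 | 21.0% | 25.4% |
| 9 | 0.7 | 17.5% | 19.5% |

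The range is about 16 to 30%. A repeat with 60,000 runs moved no entry by more than one percentage point. With independent measures the top value is about 33%.

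**5. Power if all primaries stay.** The strictest Holm step equals Bonferroni. At d = 0.67 with 35 completers per group:

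| Primaries | Alpha | Power | Completers for 80% | Per group after 30% attrition |
|---|---|---|---|---|
| 7 | 0.0071 | 54% | 56 | 80 |
| 8 | 0.00625 | 53% | 58 | 83 |
| 9 | 0.0056 | 51% | 59 | 85 |

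One named primary at 0.05 keeps 80% with 50 per group.

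**The case against.** The strongest reply is that the plan does not test each measure directly. A reader might infer from seven to nine outcomes at 0.05 that the trial has a 17 to 37% chance of a false primary result even if exercise does nothing. The Data analysis section does not support that: one-way ANOVAs follow only a significant interaction, and with that step the rate under no effect is about 3 to 5% per MANOVA. The reply stands. The higher range applies only if measures are in practice tested one by one or in separate MANOVAs. The article does not say how many MANOVAs are run, or on which outcomes. One MANOVA over all primaries cannot serve every visit, because the performance tests stop after one year.

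A reader might also infer that pain's status was left open so that it could be settled after seeing the data. The text does not show this. The abstract's verb can be read as non-exhaustive, and the methods place the pain scales among the primaries. What stands is an inconsistency that is easily corrected.

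It can also be said that a multivariate test across domains is a recognised way to handle several co-equal outcomes, that a condensed article may leave the post-hoc method to a fuller document, and that testing secondary measures is compatible with building hypotheses. All three are fair. But a post-hoc method for pairwise comparisons does not by itself adjust across outcomes, and the article states a single level for every test.

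**Conclusion.** The concern holds in a conditional form. The lists conflict (seven against eight or nine), no measure or visit is decisive, and no adjustment across outcomes is stated. The MANOVA keeps error near 5% per MANOVA only when nothing differs. If one measure truly responds, the chance of at least one false positive primary result among the others is about 16 to 30% at one visit.

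That size rests on assumptions the article does not fix: 35 completers per group, one MANOVA over all primaries approximated by a single-visit test, a true effect of 0.67 to 1.2 SD on one measure and none on the rest, and outcome correlations of 0.3 to 0.7. More visits or more MANOVAs would raise it. The documents do not support a claim that secondary measures may not be tested, or that one particular questionnaire has to be the primary outcome.

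**What to change.** 1. Make the primary list identical in the abstract and in the section on primary outcome measures. State whether the pain scales are primary and, if so, whether they count as one measure or two.
2. Before unblinding, choose one of two routes:
   - name one primary outcome and one visit, tested at 0.05, with all other measures secondary; or
   - keep the fixed list and apply Holm across it at one named visit after the MANOVA. In simulation this kept the error among unaffected measures at or below 5%.
3. Label tests on secondary measures as exploratory, in line with how the Outcome measures section describes them.

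The cost is wording, plus stricter thresholds for measures not named primary. The first route leaves the 50 per group unchanged. Under the second, power for a measure at the strictest step falls from 80% to about 51 to 54% at d = 0.67; restoring 80% at that step would need 80 to 85 per group.
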